## 4.2 Exclusion criteria

Subjects should not enter the study if any of the following exclusion criteria are fulfilled:

- 1 Involvement in the planning and/or conduct of the study (applies to both AstraZeneca staff and/or staff at the study site). Previous enrolment in the present study,
- 2 Participation in another clinical study with an investigational product during the last 4 weeks,
- 3 Any previous treatment with a PD1 or PD-L1 inhibitor, including durvalumab or an anti-CTLA4, including tremelimumab (Unless prior PD1/PD-L1 or CTLA-4 inhibition is a specific entry criterion)
- 4 History of another malignancy within the 5 previous years with low potential risk for recurrence other than :
  - *Adequately treated non-melanoma skin cancer or lentigo maligna without evidence of disease*
  - *Adequately treated carcinoma in situ without evidence of disease eg, cervical cancer in situ*
- 5 Receipt of the last dose of anti-cancer therapy (chemotherapy, immunotherapy, endocrine therapy, targeted therapy, biologic therapy, tumor embolization, monoclonal antibodies, other investigational agent) 28 days prior to the first dose of study drug (14 days prior to the first dose of study drug for subjects who have received prior TKIs (e.g., erlotinib, gefitinib and crizotinib) and within 6 weeks for nitrosourea or mitomycin C).
- 6 Mean QT interval corrected for heart rate (QTc)  $\geq 470$  ms calculated from 3 electrocardiograms (ECGs) using Frediricia's Correction,
- 7 Current or prior use of immunosuppressive medication within 28 days before the first dose of durvalumab or tremelimumab, with the exceptions of intranasal and inhaled corticosteroids or systemic corticosteroids at physiological doses, which are not to exceed 10 mg/day of prednisone, or an equivalent corticosteroid
- 8 Any history of hypersensitivity to durvalumab, tremelimumab, FOLFOX or their excipients,
- 9 Any unresolved toxicity (CTCAE grade  $>1$ ) from previous anti-cancer therapy. Subjects with irreversible toxicity that is not reasonably expected to be exacerbated by the investigational product may be included (e.g., hearing loss, peripherally neuropathy)
- 10 Any prior Grade  $\geq 3$  immune-related adverse event (irAE) while receiving any previous immunotherapy agent, or any unresolved irAE  $>$ Grade 1 ,

- 11 Active or prior documented autoimmune disease within the past 2 years NOTE: Subjects with vitiligo, Grave's disease, or psoriasis not requiring systemic treatment (within the past 2 years) are not excluded,
- 12 Active or prior documented inflammatory bowel disease (e.g., Crohn's disease, ulcerative colitis),
- 13 History of primary immunodeficiency,
- 14 History of organ transplant that requires use of immunosuppressive,
- 15 History of allogeneic organ transplant,
- 16 Uncontrolled intercurrent illness including, but not limited to, ongoing or active infection; Clinically significant cardiovascular disease including: myocardial infarction within 6 months,, symptomatic congestive heart failure, uncontrolled hypertension, unstable angina pectoris, cardiac arrhythmia; history of Mobitz II second degree or third degree heart block without a permanent pacemaker in place, hypotension,; rest limb claudication or ischemia within 6 months; active peptic ulcer disease or gastritis, active bleeding diatheses including any subject known to have evidence of acute or chronic hepatitis B, hepatitis C or human immunodeficiency virus (HIV), or psychiatric illness/social situations that would limit compliance with study requirements or compromise the ability of the subject to give written informed consent,
- 17 Sever concurrent disease, or co-morbidity that in the judgment of the investigator, would make the patient inappropriate for enrolment,
- 18 Ongoing treatment with CYP3A4 substrates or regularly taking of grapefruit juice,
- 19 Known history of active tuberculosis,
- 20 History of leptomeningeal carcinomatosis,
- 21 Brain metastases or spinal cord compression,
- 22 Receipt of live attenuated vaccination within 30 days prior to study entry or within 30 days of receiving durvalumab or tremelimumab
- 23 Female subjects who are pregnant, breast-feeding or male or female patients of reproductive potential who are not employing an effective method of birth control,
- 24 Any condition that, in the opinion of the investigator, would interfere with evaluation of study treatment or interpretation of patient safety or study results,
- 25 Symptomatic or uncontrolled brain metastases requiring concurrent treatment, inclusive of but not limited to surgery, radiation and/or corticosteroids,
- 26 Subjects with uncontrolled seizures,
- 27 Female patients who are pregnant or breastfeeding or male or female patients of reproductive potential who are not willing to employ effective birth control from screening to 180 days after the last dose of durvalumab + tremelimumab combination therapy or 90 days after the last dose of durvalumab monotherapy, whichever is the longer time period
- 28 Known allergy or hypersensitivity to IP or any excipient
- 29 Patients with tumors that invade major vessels, as shown unequivocally by imaging studies

- 30 Patients with central lung metastases (i.e within 2 cm from the hilum) that are cavitory as shown unequivocally by imaging studies
- 31 Patients with any prior history of bleeding related to the current colorectal cancer
- 32 Patients with a history of gross hemoptysis (bright red blood of ½ teaspoon or more per episode of coughing) ≤ 3 months prior to enrollment
- 33. Patients with a recurrence delay smaller than 6 months after the adjuvant chemotherapy.
- 34. Patients with resectable disease

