## 4. PATIENT SELECTION, ENROLLMENT, RESTRICTIONS, DISCONTINUATION AND WITHDRAWAL

Each patient must meet all of the inclusion criteria (Section 4.1) and none of the exclusion criteria (Section 4.2) for this study. Under no circumstances, will there be exceptions to this rule.

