| Creatinine CL
(mL/min) | $\frac{\text{Weight (kg)} \times (140 - \text{Age})}{72 \times \text{serum creatinine (mg/dL)}}$ | $\frac{\text{Weight (kg)} \times (140 - \text{Age})}{72 \times \text{serum creatinine (mg/dL)}} \times 0.85$ |

- 9 Tumour evaluation (CT scan) in the previous 4 weeks with presence of at least one measurable lesion according to RECIST 1.1 criteria,
- 10 At least 4 weeks since the last chemotherapy, immunotherapy or other drug therapy and / or radiotherapy,
- 11 Recovery to grade  $\leq 1$  from any adverse event (AE) derived from previous treatment according to the criteria of the National Cancer Institute Common Terminology Criteria for Adverse Events (NCI-CTCAE) version 4.0,
- 12 - For principal study: willingness to provide consent for use of archived tissue with sufficient material available for analysis.  
For ancillary study: Metastasis should be accessible to performed biopsy

- 13 Female subjects must either be of non-reproductive potential (ie, post-menopausal by history:  $\geq 60$  years old and no menses for  $\geq 1$  year without an alternative medical cause; OR history of hysterectomy, OR history of bilateral tubal ligation, OR history of bilateral oophorectomy) or must have a negative serum pregnancy test upon study entry,
- 14 Patients must be affiliated to a social security system,
- 15 Subject is willing and able to comply with the protocol for the duration of the study including undergoing treatment and scheduled visits and examinations including follow up.

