## Evaluation of target lesions

|                         |                                                                                                                                                                                        |
|-------------------------|----------------------------------------------------------------------------------------------------------------------------------------------------------------------------------------|
| Complete Response (CR): | Disappearance of all target lesions.                                                                                                                                                   |
| Partial Response (PR):  | At least a 30% decrease in the sum of LD of target lesions taking as reference the baseline sum LD.                                                                                    |
| Progression (PD):       | At least a 20% increase in the sum of LD of target lesions taking as references the smallest sum LD recorded since the treatment started or the appearance of one or more new lesions. |
| Stable Disease (SD):    | Neither sufficient shrinkage to qualify for PR nor sufficient increase to qualify for PD taking as references the smallest sum LD since the treatment started.                         |

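### Exclusion 4 is worded backwards: taken literally it bars only low-recurrence-risk second cancers, and leaves a recent high-risk one to investigator judgment

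*Protocol*

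**What the plan says.** Exclusion 4 has the same wording in the synopsis (Exclusion Criteria) and in section 4.2. It bars a "History of another malignancy within the 5 previous years with low potential risk for recurrence other than" two listed types:

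- The first exemption is for skin lesions: "Adequately treated non-melanoma skin cancer or lentigo maligna without evidence of disease".
- The second exemption is for pre-invasive lesions: "Adequately treated carcinoma in situ without evidence of disease eg, cervical cancer in situ".

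The opening of section 4 requires each patient to meet every inclusion criterion and no exclusion criterion, and adds: "Under no circumstances, will there be exceptions to this rule".

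Two other items could bear on a patient with a second cancer, both by opinion. Exclusion 24 covers "Any condition that, in the opinion of the investigator, would interfere with evaluation of study treatment or interpretation of patient safety or study results". Exclusion 17 covers severe concurrent disease or "co-morbidity that in the judgment of the investigator, would make the patient inappropriate for enrolment".

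On outcomes, the target-lesion table in section 9.1.2 defines progression as a 20% increase "or the appearance of one or more new lesions", and the comparison table in section 9.2 treats new lesions as progression without exception under RECIST 1.1. Sections 9.3 and 9.4 count death from any cause in PFS (absent progression) and in OS.

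**The concern.** An exclusion for other malignancies protects the endpoints from events caused by a different cancer. For that it must keep out the cancers most likely to come back. As written, item 4 names only those least likely to.

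The trial has no control arm in which such events would also occur. A relapse of the other cancer that appears as a new lesion would be recorded as progression on the study regimen, and a death from it would count in both PFS and OS. Because the error sits in an operative eligibility rule, and section 4 forbids exceptions, sites cannot quietly apply the intended rule in its place. A pre-enrolment check against the text would find no violation in a patient with a recent high-risk second cancer.

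**Working it through.** This is mainly a check of text.

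**1. Parse item 4 and compare it with the two possible repairs.** A closed list deletes the low-risk qualifier. An open class moves it into the exception, with the two named types as examples. The patients are hypothetical.

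| Other malignancy | Item 4 as written | Closed list | Open class |
|---|---|---|---|
| Treated skin or in situ type named in the item, within 5 years | not excluded | not excluded | not excluded |
| Another type, low recurrence risk, 4 years ago | excluded | excluded | not excluded |
| Invasive, high recurrence risk, 1 year ago | **not excluded** | excluded | excluded |
| Any type, more than 5 years ago | not excluded | not excluded | not excluded |

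The third row is wrong under either repair. The second row is wrong only if the open class was meant.

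**2. Infer the purpose.** Both exceptions are low-risk cancers. A rule that exempts low-risk cancers and is otherwise aimed only at low-risk cancers has no sensible purpose in a trial with PFS and OS endpoints. The synopsis repeats the wording, so nothing elsewhere corrects it.

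**3. Look for another criterion that closes the gap** (inclusions 1 to 15, exclusions 1 to 34).

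- Inclusion 10, "At least 4 weeks since the last chemotherapy, immunotherapy or other drug therapy and / or radiotherapy", and exclusion 5 are washout rules. They stop a patient treated very recently, not one treated a year ago.
- Inclusion 7 requires a life expectancy above 12 weeks. It does not refer to a second cancer.
- Exclusions 17 and 24 could apply, at the discretion of investigators across 9 sites.
- No other item names a second malignancy.

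So no objective criterion excludes the patient in the third row.

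**4. Check that the decision rule itself is unaffected.** Inputs: continue with 9 or more of 16, then 27 more patients (section 11.3.4); success with 26 or more of 43 (section 11.3.2); rates of 50% and 70.7% at 3 months (section 11.4). The probability of success at rate p is

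P(p) = Σ over x = 9 to 16 of b(x; 16, p) × Pr[Bin(27, p) ≥ 26 − x].

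- P(0.50) = 0.093, against the stated α of 10%.
- P(0.707) = 0.901, against the stated power of 90%.

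The plan's figures are reproduced, and item 4 does not enter the formula.

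**5. Illustration only, on assumptions that are not in the protocol.** Suppose k of the 43 evaluable patients have such a history and a 3-month success probability q instead of 0.707. The average rate is [(43 − k) × 0.707 + k × q] / 43. For k = 1 and q = 0 this is 42 × 0.707 / 43 = 0.691.

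| k | Chance of success, q = 0 | Chance of success, q = 0.50 |
|---|---|---|
| 0 | 0.90 | 0.90 |
| 1 | 0.86 | 0.89 |
| 2 | 0.81 | 0.88 |
| 3 | 0.75 | 0.87 |

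The q = 0 column is an extreme: every such patient would have to fail by 3 months.

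**The case against.** The strongest reply is that this is a misplaced phrase which an oncologist would read correctly. The exceptions make the intention plain, and failing to meet item 4 does not make a patient eligible. Exclusion 24 bars exactly the kind of condition that would cloud interpretation of the results, exclusion 17 covers serious co-morbidity, the washout rules stop anyone under current treatment, and section 6.1.2 provides for a check of criteria before inclusion. For harm to follow, such a patient must pass all of these, the other cancer must relapse or kill during the trial, and the event must be counted against the regimen.

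Much of this stands. A reader might infer that a patient with a recent high-risk cancer would be admitted. The protocol does not support that: the patient is not excluded by item 4 or by any objective rule, but may well be stopped by judgment. A reader might also infer that one misattributed progression would reverse the trial's conclusion, since 25 of 43 fails and 26 passes. That is true of any fixed cut-off and is not evidence about this item.

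What does not stand is leaving the sentence as it is. An objective 5-year rule exists so that eligibility does not depend on opinion from site to site, and section 4 tells sites to apply the criteria without exception.

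**Conclusion.** Item 4 says the reverse of its evident purpose, in both places where it appears. This is a drafting error in an operative eligibility rule that should be corrected. It is not a flaw in the sample size or the decision rule, whose error rates stay at 0.093 and 0.901.

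The consequence is that a recent high-risk second malignancy is left to investigator judgment, so that its relapse, or a death from it, could be scored against the regimen. The size cannot be established: the protocol gives no count of such patients, and it may be zero. The illustrative power figures rest entirely on assumed counts and success rates and should not be cited as an estimated bias.

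A reader might also conclude that the wording needlessly turns away suitable low-risk patients. That holds only if an open low-risk exception was intended. Under a closed list those patients are excluded on purpose, and the protocol does not show which was meant.

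**What to change.** Correct item 4 in the synopsis and in section 4.2 so that it excludes any other malignancy within the previous 5 years apart from the low-risk exceptions. There are two ways to do this, and the sponsor should state which was meant:

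- **Closed list:** delete the low-recurrence-risk qualifier. Only the two named types are then exempt.
- **Open class:** move the qualifier into the exception, so that malignancies with low recurrence risk are exempt and the two named types serve as examples.

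The closed list is fully objective. The open class leaves some judgment about what counts as low risk.

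The cost is one amended sentence in two places and a small loss of eligible patients. Under either version, patients with a recent higher-risk second cancer become ineligible by rule. Under the closed list, other low-risk cancers also remain excluded, as they are now. No change to the sample size or the Simon boundaries is needed.

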### **4.3 Withdrawal of Subjects from Study Treatment and/or Study**

An individual subject will not receive any further Durvalumab or Tremelimumab products if any of the following occur in the subject in question:

- 1. Withdrawal of consent or lost to follow-up
- 2. Adverse event that, in the opinion of the investigator or the sponsor, contraindicates further dosing
- 3. Subject is determined to have met one or more of the exclusion criteria for study participation at study entry and continuing investigational therapy might constitute a safety risk
- 4. Pregnancy or intent to become pregnant
- 5. Any AE that meets criteria for discontinuation
- 6. Dose-limiting toxicity
- 7. Grade ≥ 3 infusion reaction
- 8. Subject noncompliance that, in the opinion of the investigator or sponsor, warrants withdrawal; eg, refusal to adhere to scheduled visits
- 9. Initiation of alternative anticancer therapy including another investigational agent
- 10. Confirmation of PD and investigator determination that the subject is no longer benefiting from treatment with durvalumab

Subjects who are permanently discontinued from further receipt of investigational product, regardless of the reason (withdrawal of consent, due to an AE, other), will be identified as having permanently discontinued treatment.

Subjects who are permanently discontinued from receiving investigational product will be followed for safety per Section 10.0 unless consent is withdrawn or the subject is lost to follow-up or enrolled in another clinical study, in these cases, all study procedure will be stopped. All subjects will be followed for survival. Subjects who decline to return to the site for evaluations will be offered follow-up by phone every 4 months as an alternative.

#### **Withdrawal of consent**

If consent is withdrawn, the subject will not receive any further investigational product or further study observation.

## **4.4 Replacement of subjects**

Efficacy analyses will be performed in modified ITT, ie including all patients following the major inclusion criteria. Other patients will be replaced (anticipated dropout rate of 10%).

## **5. INVESTIGATIONAL PRODUCT(S)**

### **5.1 Durvalumab and tremelimumab**

The Investigational Products Supply section of AstraZeneca/MedImmune will supply durvalumab and tremelimumab to the investigator as a solution for infusion after dilution.

#### **5.1.1 Formulation/packaging/storage**

##### **Durvalumab**

Durvalumab will be supplied by AstraZeneca as a 500-mg vial solution for infusion after dilution. The solution contains 50 mg/mL durvalumab, 26 mM histidine/histidine-hydrochloride, 275 mM trehalose dihydrate, and 0.02% (weight/volume) polysorbate 80; it has a pH of 6.0. The nominal fill volume is 10 mL. Investigational product vials are stored at 2°C to 8°C (36°F to 46°F) and must not be frozen. Durvalumab must be used within the individually assigned expiry date on the label.

##### **Tremelimumab**

Tremelimumab will be supplied by AstraZeneca as a 400-mg or a 25mg vial solution for infusion after dilution. The solution contains 20 mg/mL of tremelimumab, 20 mM histidine/histidine hydrochloride, 222 mM trehalose dihydrate, 0.02% (w/v) polysorbate 80, and 0.27 mM disodium edetate dihydrate (EDTA); it has a pH of 5.5 and density of 1,034 g/mL. The nominal fill volume is 20 mL for the 400mg and 1,25mL for the 25mg vial. Investigational product vials are stored at 2°C to 8°C (36°F to 46°F) and must not be frozen. Tremelimumab must be used within the individually assigned expiry date on the label.

### **5.2 Dose and treatment regimens**

#### **5.2.1 Treatment regimens**

##### **Durvalumab + tremelimumab**

Patient will receive 750mg durvalumab via IV infusion q2w for up to 8 doses/cycles and 75 mg tremelimumab via IV infusion q4w for up to 4 doses/cycles, and then continue 750mg durvalumab q2w starting on Week 16 for up to 20 months (40 doses). Dosing outside the window should be discussed with the Study Physician. Tremelimumab will be administered first. Durvalumab infusion will start approximately 1 hour after the end of tremelimumab infusion. The duration will be approximately 1 hour for each infusion. A 1-hour observation period is required after the first infusion of durvalumab and tremelimumab. If no clinically significant infusion reactions are observed during or after the first cycle, subsequent infusion observation periods can be at the Investigator's discretion.

(suggested 30 minutes after each durvalumab and tremelimumab infusion). FOLFOX will be administered last and will be delivered as standard practice q2w.

## **5.2.2 Duration of treatment and criteria for retreatment**

**Treatment will be delivered with a maximum of 24 months:**

- 4 months with the association Durvalumab + Tremelimumab + FOLFOX (M1 to M4)
- 20 months of maintenance with Durvalumab alone (M5 to M24)

Retreatment is allowed (**once only**) for patients meeting the retreatment criteria below. The same treatment guidelines followed during the initial 24-month (4 months with the association + 20 months maintenance) treatment period will be followed during the retreatment period, including the same dose and frequency of treatments and the same schedule of assessments.

Patients may undergo retreatment in 1 clinical scenarios, described below:

1. Patients who complete the 4 dosing cycles of the combination of durvalumab and tremelimumab portion of the regimen (with clinical benefit per Investigator judgment), but subsequently have evidence of PD during the durvalumab monotherapy portion of the combination regimen, with or without confirmation according to RECIST 1.1, may restart treatment with the combination (FOLFOX + Durvalumab + Tremelimumab).

Before restarting their assigned treatment, the Investigator should ensure that the patient :

- does not have any significant, unacceptable, or irreversible toxicities that indicate continuing treatment will not further benefit the patient.
- Still fulfils the eligibility criteria for this study, to restart folfox, durvalumab and tremelimumab.
- Has not received an intervening systemic anticancer therapy after their assigned treatment discontinuation.
- Has to perform a baseline tumor assessment within 28 days of restarting their assigned treatment; all further scans should occur with the same frequency as during the initial 12 months of treatment (relative to the date of randomization) until study treatment is stopped (maximum of 12 months of further treatment).

During the retreatment period, patients receiving durvalumab + tremelimumab may resume durvalumab dosing at 750mg q2w with 75 mg of tremelimumab q4w for 4 doses each and combined to FOLFOX for 3 months. Patients will then continue with durvalumab monotherapy at 750 mg q2w, until month 24 if no PD is observed.

Treatment through 24 months is at the Investigator's discretion, and the Investigator should ensure that patients do not have any significant, unacceptable, or irreversible toxicity that indicate that continuing treatment will not further benefit the patient. A patient with a confirmed progression receiving durvalumab + tremelimumab cannot continue therapy or obtain retreatment if dosing is ongoing in the combination portion of therapy (**q4w dosing**) and progression occurs in a target lesion that has previously shown a confirmed response.

Patients who AstraZeneca and/or the Investigator determine may not continue treatment will enter follow-up.

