| QLQ-C30 and QLQ-CR29                                                                                                                  | X                          |                                                  | X  |    |    |    | X  |    |    |
| Durvalumab (750 mg)                                                                                                                   |                            | X                                                | X  | X  | X  | X  | X  | X  | X  |
| Tremelimumab (75mg)                                                                                                                   |                            | X                                                |    | X  |    | X  |    | X  |    |
| FOLFOX administration                                                                                                                 |                            | X                                                | X  | X  | X  | X  | X  |    |    |

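### Section 5.2.2 gives a retreatment dose count that contradicts the initial schedule and two duration limits that conflict for restarts before month 12; FOLFOX and 5-FU length also differ between sections

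*Protocol*

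**What the plan says.** **Retreatment doses.** Section 5.2.2 opens the retreatment paragraph with a general rule: "The same treatment guidelines followed during the initial 24-month (4 months with the association + 20 months maintenance) treatment period will be followed". It then gives a specific instruction: patients "may resume durvalumab dosing at 750mg q2w with 75 mg of tremelimumab q4w for 4 doses each and combined to FOLFOX for 3 months", after which they move to durvalumab alone. The initial course in Section 5.2.1 is "750mg durvalumab via IV infusion q2w for up to 8 doses/cycles and 75 mg tremelimumab via IV infusion q4w for up to 4 doses/cycles", with durvalumab alone from week 16 for 40 doses. Figure 1a agrees: durvalumab at V1 to V8, tremelimumab at V1, V3, V5 and V7.

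**Retreatment length.** The bullet on scans in Section 5.2.2 runs "until study treatment is stopped (maximum of 12 months of further treatment". The paragraph below it says: "Patients will then continue with durvalumab monotherapy at 750 mg q2w, until month 24 if no PD is observed".

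**FOLFOX length.** In Figure 1a the row "FOLFOX administration" is marked at V1 to V6 and blank at V7 and V8. Section 5.2.2 describes "4 months with the association Durvalumab + Tremelimumab + FOLFOX (M1 to M4"). Section 5.3.2 expects between 1 and 12 cycles and equates this with 6 months. In Section 6.2.2, under laryngopharyngeal dysesthesia, a patient who stops oxaliplatin for neurotoxicity continues 5-FU and leucovorin, or capecitabine, for a period of 3 or 6 months said to be fixed by randomisation. The synopsis describes the study as non-randomised.

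**The concern.** These are operative dosing instructions. Section 6.2.3 says that the triple combination has not been evaluated before, and retreatment exposes a patient to all of it a second time. A site should be able to read off one dose count, one FOLFOX length and one stopping date.

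It cannot do so here. A specific sentence contradicts the general rule above it, two duration limits in one section can give different end dates, and one duration depends on an allocation that no patient in this trial has. At stake are the treatment given during retreatment and after an oxaliplatin stop, and possibly membership of the per-protocol set, which Section 11.3.2 defines by receipt of every planned dose.

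**Working it through.** **1. Initial schedule (Section 5.2.1, Figure 1a).** Dose k falls at week interval × (k − 1).
- Durvalumab, 8 doses every 2 weeks: weeks 0, 2, 4, 6, 8, 10, 12, 14. The next dose is at week 16, as the protocol states.
- Tremelimumab, 4 doses every 4 weeks: weeks 0, 4, 8, 12.
- Total durvalumab: 8 + 40 = 48 doses, which matches Cycle 48 in Section 8.1.3.

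The initial schedule is internally consistent.

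**2. Retreatment sentence, read literally.**
- Four durvalumab doses every 2 weeks: weeks 0, 2, 4, 6.
- Four tremelimumab doses every 4 weeks: weeks 0, 4, 8, 12.

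The two sets of four end 6 weeks apart, and only 2 of the 4 tremelimumab doses fall by week 6. Durvalumab alone cannot start at week 8, because tremelimumab is still due at weeks 8 and 12. If it starts only after the last tremelimumab dose, the sentence gives no instruction for durvalumab at weeks 8, 10 and 12. The general rule points to 8 durvalumab doses (last at week 14, alone from week 16), which is not the count the sentence gives.

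**3. Retreatment length.** Month 24 is counted from first dose, as in Section 5.2.2's own M5 to M24, Figure 1b and Section 8.1.3. A restart at month m then leaves 24 − m months; the cap allows 12.

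| Restart month | To month 24 | Cap | Excess over cap |
|---|---|---|---|
| 5 | 19 | 12 | 7 |
| 6 | 18 | 12 | 6 |
| 8 | 16 | 12 | 4 |
| 12 | 12 | 12 | 0 |
| 18 | 6 | 12 | none |
| 20 | 4 | 12 | none |

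For restarts before month 12 the two limits disagree. From month 12 onwards, stopping at month 24 satisfies both.

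**4. FOLFOX and 5-FU.**
- Figure 1a: 6 cycles at weeks 0 to 10, about 3 months. Retreatment sentence: 3 months, so the same length.
- Section 5.3.2: up to 12 cycles. At 85 mg/m² of oxaliplatin per cycle, 6 × 85 = 510 mg/m² and 12 × 85 = 1,020 mg/m².
- Section 6.2.2: 3 or 6 months of 5-FU/leucovorin, that is 6 or 12 two-weekly cycles, with nothing in this trial to decide between them.

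**5. Effect on the primary evaluation.** Retreatment requires progression during durvalumab alone, so it starts after month 4. FOLFOX covers the first 3 months on every reading. The 3-month evaluation is therefore not touched.

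**The case against.** The best defence is that these are drafting residues with an evident meaning. The general rule in Section 5.2.2 keeps dose and frequency as in the initial course, and the section elsewhere speaks of four cycles of the combination and labels that portion as four-weekly, so 8 plus 4 was probably meant. Durvalumab continues every 2 weeks and tremelimumab is four doses in any case. Taking whichever limit falls first reconciles the 12-month cap with month 24. Twelve FOLFOX cycles may be 6 initial plus 6 in retreatment, and the four-month label may simply name the phase.

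Most of this limits the consequences, and it stands to that extent. It does not remove the contradictions: the specific sentence still gives a different count, no text says that the earlier limit governs, Section 5.3.2 does not mention retreatment, and the randomisation clause has no valid meaning here.

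Four stronger readings are tempting and not supported:
- *Immunotherapy exposure differs between readings.* It does not if two-weekly dosing continues, as the text implies.
- *The stopping rule becomes ambiguous at the V6 scan.* The bar on continuing after progression applies "if dosing is ongoing in the combination portion of therapy" and V6 (week 10) lies between weeks 6 and 12. But the rule concerns confirmed progression, and Section 9 puts confirmation at least 4 weeks later, so at week 14 or after. That is past both ends.
- *Month 24 might mean 24 months from restart.* The protocol's own month numbering runs from first dose.
- *The two limits agree only for a restart at month 12.* Both are upper limits, so later restarts satisfy both.

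**Conclusion.** The point holds as an inconsistency in treatment instructions, of minor to moderate severity.

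- The retreatment count contradicts the 8 plus 4 schedule. Assuming durvalumab continues every 2 weeks, this changes no dose given.
- The retreatment limits conflict only for restarts before month 12, by up to about 7 months of durvalumab for the earliest restarts. This assumes that month 24 runs from first dose.
- FOLFOX is clearly six cycles in Figure 1a, and Section 5.3.2 allows twice that without explanation. A reader might infer that 510 and 1,020 mg/m² are rival versions of one plan; they may equally be one course and two.
- After an oxaliplatin stop, the 5-FU/leucovorin period is 3 or 6 months with no basis for choosing.
- The per-protocol set could be affected if 12 cycles were read as the plan, but that set is used only for repeat analyses.

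The primary evaluation, alpha, power and sample size do not depend on any of this.

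**What to change.** - **Section 5.2.2, retreatment doses.** Replace the dose count and FOLFOX phrase with: *8 doses of durvalumab q2w and 4 doses of tremelimumab q4w, with FOLFOX q2w for 6 cycles; durvalumab monotherapy from week 16 of retreatment*.
- **Section 5.2.2, retreatment length.** State one limit, for example: *until 12 months after restart or month 24 from first dose, whichever comes first*. The sponsor has to choose, since the protocol does not show which limit was meant.
- **Section 5.3.2.** State 6 cycles per course, with 12 reached only by a retreated patient.
- **Section 6.2.2.** Delete the capecitabine option and replace the randomisation clause with: *up to cycle 6 of the current course (initial or retreatment)*.

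The cost is wording in three sections, with no added patients, visits or procedures. If the change counts as substantial, Section 12.4 requires an amendment with ethics committee approval and, where applicable, that of the national authority.
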